**Immunogenicity Assays**

|                                          |                                                         |
|------------------------------------------|---------------------------------------------------------|
| Anti-AAV9 antibody
Anti-PGRN antibody | AAV9 Enzyme-linked immunospot (ELISpot)
PGRN ELISpot |
|------------------------------------------|---------------------------------------------------------|

**Endocrinology**

|                                           |                     |
|-------------------------------------------|---------------------|
| Follicle-stimulating hormone  | Free thyroxine (T4) |
| TSH                                       |                     |

1. A follicle-stimulating hormone test will be performed at Screening for women who are post-menopausal with spontaneous amenorrhea for at least 2 years, to confirm their post-menopausal status at Screening.

**Sirolimus Monitoring**

|                                 |
|---------------------------------|
| Sirolimus trough concentrations |
|---------------------------------|

**Hematology**

|                                                      |                      |
|------------------------------------------------------|----------------------|
| Hematocrit                                           | Hemoglobin           |
| Platelets                                            | Red blood cell count |
| White blood cell count and differential  |                      |

1. Manual microscopic review is performed only if white blood cell count and/or differential values are out of reference range.

**Coagulation**

|                                |                                       |
|--------------------------------|---------------------------------------|
| International normalized ratio | Activated partial thromboplastin time |
|--------------------------------|---------------------------------------|

**Urinalysis**

|                    |                         |
|--------------------|-------------------------|
| Bilirubin          | Blood                   |
| Glucose            | Ketones                 |
| Leukocyte esterase | Microscopy  |
| Nitrite            | pH                      |
| Protein            | Specific gravity        |
| Urobilinogen       |                         |

1. Microscopy is performed only as needed based on positive dipstick test results.

**Serology**

|                             |                      |
|-----------------------------|----------------------|
| hepatitis B surface antigen | hepatitis C antibody |
| HIV 1/2                     | MTB test             |

**Drug Screening**

|              |                 |
|--------------|-----------------|
| Opiates      | Benzodiazepines |
| Amphetamines | Cocaine         |
| Barbiturates | Phencyclidine   |

**Pregnancy Testing**

|                                                          |                              |
|----------------------------------------------------------|------------------------------|
| Serum $\beta$ -human chorionic gonadotropin  | Urine pregnancy  |
|----------------------------------------------------------|------------------------------|

1. A serum pregnancy test will be performed at Screening and for any positive urine pregnancy tests. Urine pregnancy tests will be performed at Day -1 or Day 0 (before investigational product administration), and every 3 months for the first 12 months, for women of childbearing potential.

Additional blood or urine samples may be taken at the discretion of the Investigator if the results of any test fall outside the reference ranges, or clinical symptoms necessitate additional testing to monitor patient safety. Where the clinical significance of abnormal laboratory results is considered uncertain, Screening laboratory tests may be repeated per discretion of the Investigator before dosing to confirm eligibility. If there is an alternative explanation for a positive urine or blood test for drugs of abuse (e.g., previous occasional intake of a medication or food containing for example codeine, or opiates), the test may be repeated to confirm washout.

After dosing, in the event of unexplained abnormal clinically significant laboratory test values, the tests should be repeated and followed up until they have returned to the normal range and/or an adequate explanation of the abnormality is found.

Any abnormal laboratory test results (hematology, blood chemistry, or urinalysis) or other safety assessments (e.g., ECGs, radiological scans, vital sign measurements), including those that worsen from baseline, thought to be clinically significant in the medical and scientific judgment of the Investigator are to be recorded as AEs or SAEs. All events (occurring after Screening) of ALT or AST  $>3 \times \text{ULN}$  and bilirubin  $>2 \times \text{ULN}$  ( $>35\%$  direct bilirubin) or ALT or AST  $>3 \times \text{ULN}$  and international normalized ratio  $>1.5$ , which may indicate severe liver injury (possible Hy's Law), must be reported as an SAE.

However, any clinically significant safety assessments that are associated with the underlying disease, unless judged by the Investigator to be more severe than expected for the patient's condition, are **not** to be reported as AEs or SAEs.

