reactions in spite of prophylactic corticosteroid treatment, a consultation with clinical immunologist should be considered. Immune response to the transgene protein (PGRN) is not expected in heterozygous haploinsufficient patients, as they naturally express PGRN at approximately 50% of normal levels.

Patients will receive a prophylactic steroid-sparing immunosuppressive regimen consisting of corticosteroids and sirolimus, intended to alleviate AAV9-related T-cell driven immune responses. Similar steroid-sparing approaches have demonstrated safety benefit and have been implemented in other gene therapy programs (e.g., [Bharucha-Goebel et al 2020](#); [Nevoret et al 2020](#)). Moreover, sirolimus has been shown to suppress AAV-related immune responses and increase transgene protein expression in NHPs ([Mingozzi et al 2007](#); [Ramsingh et al 2018](#)), is reported to be beneficial in animal models of FTD ([Wang et al 2012](#)), and has a manageable safety profile allowing the reduction or elimination of steroid usage ([Pidala et al 2020](#)).

Despite the beneficial effects of corticosteroids and sirolimus in the prevention and management of potential capsid and transgene immune reactions, both immunosuppressive agents are associated with a variety of adverse events (AEs). Systemic steroids at high doses can produce a variety of AEs ranging from mild irritability to life-threatening or even fatal biochemical effects including hyperglycemia, hypertension, and psychiatric disorders. A number of precautions should be considered with sirolimus usage, such as but not limited to increased risk of infections, malignancies/ lymphomas, angioedema, impaired wound healing, interstitial lung disease, hyperlipidemia, decline in renal function, proteinuria, embryo-fetal toxicity and male infertility. The use of live vaccines should be avoided during treatment with sirolimus. Sirolimus should not be used with strong CYP 3A4/P-gp inducers or inhibitors and requires monitoring of trough levels in the blood. If steroid or sirolimus side effects emerge, these drugs will be stopped or tapered as medically indicated.

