#### **5.5.1.2 Sirolimus Administration**

Patients will receive a sirolimus oral loading dose of 6 mg at Day -1. Subsequent sirolimus maintenance dose of 2 mg will be adjusted to maintain serum trough levels of 4 ng/mL (range 2 to 8 ng/mL) until the Month 3. Sirolimus will be subsequently tapered during the subsequent 15 to 30 days. Trough levels will be collected prior to administration of the sirolimus dose for each visit as presented in Schedule of Events (main study period). All sirolimus doses will be captured in the eCRF.

All patients and caregivers should be provided with a current version of the local manufacturer's medication guide, including instructions for use.

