### **5.5.2 Pre-Cisternal Puncture Procedures**

Patients will undergo standard of care medical evaluations in preparation for cisternal puncture, including anesthesiologist consultation. The neurosurgeon/interventional radiologist and anesthesiologist will review Screening clinical laboratory analyses (including documented negative pregnancy test), brain MRI and MRA, and local ECG results. Medical history and currently prescribed and over-the-counter medications will be reviewed with regards to any recent changes. At the anesthesiologist's discretion, additional clinical assessments may be performed (specific to concomitant medical conditions).

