#### **6.2.2.2 Risks Associated with the Use of Immunosuppressants**

One loading dose of 6 mg oral sirolimus will be administered at Day -1, as well as a single dose of 1 g IV methylprednisone at Day 0. A concomitant maintenance dose of 2 mg/day sirolimus will be administered orally for 90 days starting at Day 0 which will then be tapered over the ensuing 15 to 30 days. The maintenance dose is administered to achieve trough sirolimus concentration of 4 ng/mL (range 2 to 8 ng/mL). One day after treatment with PR006A, patients will start prednisone 30 mg orally for 14 days, followed by a 7-day taper. At the Investigator's discretion, adjustments of dose and duration are permitted.

Corticosteroids are administered for prophylactic suppression of inflammatory responses and to improve viral transduction. Despite the beneficial effects of prednisone and sirolimus in the prevention and management of potential liver enzyme abnormalities, systemic immunosuppressants in this dose range can produce a variety of AEs ranging from mild irritability to life-threatening or even fatal biochemical effects including but not limited to impaired wound healing, interstitial lung disease, hyperglycemia, hypertension, lymphomas/malignancies, hyperlipidemia, decline in renal function, proteinuria, embryo-fetal toxicity, and male fertility. While patients will be excluded if they are at increased risk of AEs, if corticosteroid side effects emerge, corticosteroids will be stopped or tapered as medically indicated. Glucose level checks, HbA1c, fructosamine, blood pressure, body weight, cholesterol, urine protein, lipids, red blood cell counts, neutrophil counts, protein glucose, CSF cell counts, CSF protein levels, CSF glucose levels, sirolimus trough concentrations, BMI, waist circumference, and psychosis incidence/aggravation will be monitored at study visits occurring during corticosteroid usage and after prednisone

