discontinuation. The iDMC will assess safety variables as listed for the primary safety endpoints ([Section 2](#)) and as detailed in [Section 11.1.1](#). Patients must have evidence of a negative MTB test and pneumococcal pneumonia and shingles vaccination coverage (within 10 years prior to Screening; allowed during Screening Period but at least 4 weeks prior to sirolimus loading dose) in order to initiate prednisone or sirolimus. Additionally, if medically indicated and as per local standard of care, Principal Investigators may consider performing EBV, CMV, and JC virus testing as well anti-viral (e.g., valganciclovir) and/or antibacterial (e.g., low-dose Bactrim) prophylaxis during sirolimus course.

If steroid or sirolimus side effects emerge, these drugs will be stopped or tapered as medically indicated. Details regarding additional monitoring for corticosteroid and sirolimus-related events are provided in [Section 5.5.1.3](#)

If clinically indicated and/or as per local practice, concomitant gastroprotective prophylactic medication, as well as potassium and/or calcium/vitamin D3 and bisphosphonate supplementation, may be initiated. Specifically, for patients with pre-existing osteoporosis (without history of vertebral fracture in the past year) or history of fragility fracture, the Investigator should consider prescribing appropriate therapy intended to prevent/attenuate glucocorticoid-induced osteoporosis starting at the time of initiation of prednisone administration. The same consideration to provide therapy to prevent/attenuate glucocorticoid induced osteoporosis should be given to patients whose prednisone treatment may be extended beyond 6 weeks. A dual-energy x-ray absorptiometry (DEXA) scan will be performed at Screening and will be repeated at Month 12 for patients with baseline osteopenia or osteoporosis ([Section 6.16](#)). For patients receiving prednisone for more than 3 months, HbA1c will be measured at the end of prednisone therapy.

Continued participation in the study will not be affected if the patient or Investigator finds corticosteroid administration to be intolerable or the patient develops clinically significant AEs requiring early prednisone or sirolimus discontinuation.

The following TEAEs, which may be associated with immunosuppressant regimen (see above text), should be explicitly monitored:

- Peptic ulcer disease
- Erosive gastritis

- Osteoporosis
- Increase in body weight  $\geq 5\%$  from baseline

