- c. Patients will complete Day -1 study assessments and, after the collection of blood samples, will receive a methylprednisolone pulse of 1 g IV on Day 0 (sites will be allowed to administer the methylprednisolone pulse at Day -1 depending on site preference and timing of the procedure), then prednisone 30 mg for 14 days, which will then be tapered over the ensuing 7 days. At the Investigator's discretion, higher doses or a longer taper of corticosteroids may be used ([Section 5.5.1.3](#)). A single sirolimus loading dose of 6 mg will be administered on Day 1 (with a window of Day -3 to Day -1) followed by 2 mg/day from Day 0 to Day 90 to maintain a trough level of 4 ng/mL (range 2 to 8 ng/mL). The sirolimus dose will be tapered over the next 15 to 30 days. Depending on local site requirements, patients have the option to complete an overnight inpatient stay from Day -1 to Day 0.
- d. Investigational product will be administered as a single dose into the cisterna magna via suboccipital injection by an interventional radiologist or neurosurgeon. NOTE: Prior to injection, a volume of intracisternal fluid equivalent to the PR006A dosing volume will be removed. Patients will remain under observation for 24 hours (overnight inpatient stay) after PR006A administration.
- e. Patients will be discharged on Day 1 from the study site after completion of the visit assessments.
- f. If a patient who received investigational product withdraws prematurely from the study for any reason, study site personnel should make every effort to complete the full panel of assessments scheduled for the end of treatment visit. Patients who withdraw during the treatment period will complete the Month 12 (Year 1) assessments, while patients who withdraw during the follow-up period will complete the Month 60 assessments ([Section 4.2.2](#)). If the termination visit is more than 3 months prior to the scheduled Month 12 assessment, or more than 6 months prior to the Month 60 assessment for subjects who discontinue participation after Month 12, in addition to performing termination visit assessments, the investigator and study site personnel should make every effort to complete the Month 12 or Month 60 assessments, respectively, at the originally scheduled time points.
- g. Visit window can be extended to +/- 14 days with prior Sponsor approval. All results from the prior visits must be at the site prior to the next visit.

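### The repeat urine pregnancy test is timed only against PR006A and may wait until Day 0, so a compliant site can give the sirolimus loading dose first (minor wording correction)

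*Protocol*

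**What the plan says.** **The test.** The Pregnancy Testing footnote in Section 6.5 and Table 13-1 footnote t carry the same rule: "Urine pregnancy tests will be performed at Day -1 or Day 0 (before investigational product administration"). A serum test is done at Screening, and Inclusion Criterion 15 requires it to be negative.

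**The first immunosuppressant dose.** Section 5.5.1.2 states: "Patients will receive a sirolimus oral loading dose of 6 mg at Day -1". Table 13-1 footnote c gives the load "with a window of Day -3 to Day -1". In the text at hand the nominal day in that footnote reads Day 1, but its window and the body text place the load before PR006A. Maintenance at 2 mg/day starts on Day 0.

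**Conditions for starting immunosuppression.** Section 6.2.2.2 says: "Patients must have evidence of a negative MTB test and pneumococcal pneumonia and shingles vaccination coverage", and gives the purpose as "in order to initiate prednisone or sirolimus". Pregnancy status is not among these conditions. Section 5.5.2 has the proceduralist and anesthesiologist "review Screening clinical laboratory analyses (including documented negative pregnancy test"). That check belongs to preparation for the cisternal puncture, and it refers to Screening results.

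**The hazard.** Section 1.3 includes "embryo-fetal toxicity and male infertility" among the precautions for sirolimus. Section 6.2.2.2 repeats the item for the immunosuppressants ("embryo-fetal toxicity, and male fertility").

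**The concern.** The trial excludes pregnant women and plans a repeat test shortly before dosing, but it ties that test to the second exposure of concern and not the first. If the test is positive, PR006A can be withheld, but sirolimus already swallowed cannot be taken back. What is at stake is one oral load, possibly with the first maintenance dose, in a woman who conceived after her Screening serum test. No endpoint, analysis or escalation decision is affected. The order of test and dose is a protocol matter and would not be settled in a statistical analysis plan.

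**Working it through.** The protocol gives no figure of its own to reproduce. The check compares the permitted days and then bounds the risk.

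**1. Permitted days.** The load may fall on Day -3, -2 or -1 (footnote c). The repeat test may fall on Day -1 or 0 (Section 6.5; footnote t).

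| Load | Test on Day -1 | Test on Day 0 |
|---|---|---|
| Day -1 | same day, order not stated | load first by 1 day |
| Day -2 | load first by 1 day | load first by 2 days |
| Day -3 | load first by 2 days | load first by 3 days |

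In five of the six combinations the load precedes the test. In the sixth the test can come first, but nothing requires it. The 3-day figure needs the earliest load and the latest test together. With the body-text load on Day -1, the delay is at most 1 day.

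**2. Age of the last required negative test at the load.** Screening may start on Day -35 (Table 13-1).
- Day -1 load: 35 - 1 = 34 days.
- Day -3 load: 35 - 3 = 32 days.

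These are maxima for a standard Screening Period. Footnote b allows an extension with Sponsor approval, which would lengthen them.

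**3. Chance of a pregnancy in that interval.** Inclusion Criterion 12 defines highly effective contraception by a failure rate below 1% per year with perfect use.
- Per woman over 34 days: 0.01 × 34/365 = 0.00093, so under 0.094%.
- All 15 patients of childbearing potential (upper extreme): 15 × 0.00093 = 0.0140; unrounded 0.01397, so under 0.014 expected pregnancies.
- Three such women (assumed, since the protocol gives no number): 3 × 0.00093 = 0.0028.
- Fivefold failure rate (assumed, to allow for imperfect use), all 15: 5 × 0.01397 = 0.070.

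These figures count every pregnancy arising in the interval. The number that earlier testing could reveal is smaller, because a very recent conception may not yet be detectable at the load.

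**4. Sirolimus taken before a Day 0 test.** This is 6 mg, or 6 + 2 = 8 mg if the Day 0 maintenance dose also comes first. The nominal total before taper is 6 + 90 × 2 = 186 mg (90 days, body text) or 6 + 91 × 2 = 188 mg (Day 0 to Day 90, footnote c).
- 6/186 and 6/188 are both 3.2%.
- 8/186 and 8/188 are both 4.3%.

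Maintenance is adjusted to trough, so these shares are nominal. PR006A and nearly all the sirolimus still follow the test.

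**The case against.** The strongest reply is that existing controls already cover most of this. The pregnancy-test row in Table 13-1 is marked on Day -1 as well as Day 0. Inclusion and exclusion criteria are checked again on Day -1, and Inclusion Criterion 15 bars pregnancy as such. Contraindications to sirolimus are exclusionary under Exclusion Criterion 3. Contraception is mandatory. Urinalysis and the urine drug screen are already due on Day -1, so a site has little reason to leave only the pregnancy test until Day 0. The remaining risk is negligible, and tying the test to the investigational product may be deliberate.

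Much of this stands, and it is why the point is minor. It does not close the gap. Footnote t makes Day -1 and Day 0 alternatives. The Day -1 eligibility check calls for no new test, and a load on Day -3 or Day -2 comes before that check.

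A reader might infer more than the text supports:
- **That the urine test is sure to reveal such a pregnancy.** The protocol gives no sensitivity or detection window.
- **That a 3-day delay is typical.** It is the extreme corner of the footnote c window.
- **That methylprednisolone has the same problem.** Footnote c places the Day -1 assessments and blood samples before that pulse, so it is not part of this point.

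**Conclusion.** The gap in the wording is real. A site can follow every sentence and still give the sirolimus load before the repeat pregnancy test, by 1 day in the ordinary case and by up to 3 days in the extreme one. It then relies on a Screening serum test that may be 32 to 34 days old, or older after an extension.

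The size is very small: under 0.094% per woman and under 0.014 expected pregnancies at the 15-patient extreme. Both figures rest on the protocol's perfect-use failure rate and a 34-day interval. The assumed fivefold rate raises the extreme to 0.070. A reader might take this for a major safety defect, but the figures do not support that. It is a wording correction worth making because the protocol names the hazard and the remedy costs almost nothing.

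**What to change.** In the Section 6.5 Pregnancy Testing footnote and Table 13-1 footnote t, require for women of childbearing potential a negative urine pregnancy test before the first sirolimus dose, on the day of that dose or the day before. Keep the negative test on Day -1 or Day 0 before PR006A.

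- **Load on Day -1:** one Day -1 test done before the load meets both requirements, using urine already collected that day. A site that now tests on Day 0 moves the test one day earlier.
- **Load on Day -3 or Day -2:** either move the load for these women to Day -1, after the test, or add one urine test before the earlier load. Table 13-1 has no separate visit on those days, so the added test may need an extra attendance or a home test.

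That added test, for early loads only, is the sole cost beyond rewording two footnotes. No dose, endpoint or analysis changes.

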## 6.6 Antibody/Biomarker Evaluation in Blood

Anti-AAV9 antibodies, anti-PGRN antibodies, AAV9 ELISpot, PGRN ELISpot, PGRN, NfL, and biomarkers of neuroinflammation, astroglial pathology, and lysosomal function will be measured in blood.

## 6.7 Biomarker Evaluation in Urine

Biomarkers of lysosomal function (e.g., BMP) will be measured in urine.

## 6.8 Cerebrospinal Fluid Evaluations

Anti-AAV9 antibodies, anti-PGRN antibodies, biomarkers of neurodegeneration ( ), PGRN, biomarkers of neuroinflammation, astroglial pathology, and lysosomal function as well as local assessment of cell count, protein, and glucose will be measured in CSF.

The LP and CSF collection will occur during the treatment period (Day 0; [Table 13-1](#)), with optional additional CSF collection during follow-up ([Table 13-2](#)). Patients are not required to participate in any LP procedures and CSF collections during follow-up in order to participate in the study. Patients who agree to participate in additional CSF sampling will be required to provide an additional consent (contained in the main ICF).

